### Intervention

The ToM intervention is a manualized weekly cognitive behavioral group intervention, including eight sessions of approximately 1 hour, provided to five or six children simultaneously, with a mutual age difference that does not exceed 3 years. Each session will be supervised by one or two certified therapists. The program is based on the ToM intervention developed by Steerneman [23], which included 200 optional exercises. This intervention was initially modified to a 16 session program [8,12]. For the current intervention, it was shortened to eight sessions. It is referred to as the ‘Mini ToM intervention’. The program is shortened for several reasons. While the 16-session program devoted relatively much attention to the introduction of basic emotions, most participating children already performed at ceiling level on basic emotion understanding tasks [12]. In the process of shortening the program, it was made sure that all the substages of the ToM were clearly represented in the intervention, but were balanced, while redundant repetition was prevented. Furthermore, in other domains of functioning, recent studies have demonstrated positive effects of both short-term and long-term interventions in autism [24]. Finally, the shorter intervention is likely to be more cost-effective and allows us to enroll more children in intervention studies. In this way, moderators of the intervention efficacy can be examined, aiming to determine which children benefit most from the intervention.

In general, the sessions all follow the same structure: (1) discussing the homework assignment, (2) games and exercises related to the day’s theme, (3) children summarizing the session to their parents, (4) explanation of the next week’s homework assignment. In the first session, the participants and the intervention are introduced. It is explained to the children that they will learn to perceive situations and people around them and that they will learn to adapt their behavior. Two different games allow the children to practice looking carefully at each other. Homework includes answering questions about the names of participants and trainers. In the second session, children are taught that what people like or dislike can differ from person to person. As assignments, they are asked to decide on activities for their group members and discuss gossiping, based on a short story, and learn to see objects from different perspectives (that is, through the eyes of an elephant and a mouse). Homework includes drawing the same object from different angles. In the third session, intentions play a central role. It is explained that it is frequently possible to predict people’s future actions based on their intentions. A fairy tale is read aloud and the children are questioned about intentions, thinking, feeling, and whether they can predict behavior, and children participate in a game about the differences between literal and figurative language. Homework includes reading a story with one of the parents or caregivers and answering questions about intentions, thinking, and feeling. The fourth session is about the emotions happiness, sadness, anger, and anxiety. It includes examples of facial expressions, body signals, and both hypothetical and personal, real-life examples. A collage is made of the four emotions and children are engaged in role-plays. In the homework assignment, children are stimulated to observe these emotions in their own environment. The fifth session continues with more complex emotions, for example, guilt, disappointment, and shame. After discussing personal experiences, a board game is played, in which children answer questions about emotions. In the homework assignment, children are stimulated to observe complex emotions in their own environment. In the sixth session, the children engage in a play, focusing on the difference between real and pretend, and taking the perspective of another person. The play is videotaped and shown to the children and parents. In the homework assignment, children need to interview their parents about their interests. In the seventh session, stories are read about protagonists who need to put themselves into the position of someone else (first-order belief ToM). For the homework assignment, children answer second-order belief questions about a story. In the last session, the children perform in a play about a family making a trip to the zoo. At the end of the intervention, each child receives a certificate.

### Measures of primary outcomes: conceptual skills

#### Theory of mind (ToM) test

The ToM test [25] is a standardized interview for children aged 5 to 13 years. It measures theory of mind knowledge and differentiates between three stages, with cognitive substages within each stage including perception and imitation, emotion recognition, elementary theory of mind, second-order belief understanding and understanding of complex humor. Children listen to a hypothetical story or look at a picture and answer the corresponding question. The test contains 72 items, which are scored on a 2-point scale (0 = incorrect, 1 = correct). Concurrent validity of the ToM test with traditional ToM tasks is moderate to high (*r* between 0.37 and 0.77) [25] and the test-retest reliability is high (intraclass correlation between 0.80 and 0.99) [12].

#### ToM advanced test

The ToM advanced test is a shortened version of ‘Stories from Everyday Life’ [6,26-28]. The test measures five forms of advanced theory of mind: understanding of second-order false belief, emotional display rules, violation of social rules, double bluff, and sarcasm. The children listen to a story and answer questions about mental states. Each mental state question is scored on a 3-point Likert scale (0 = incorrect, 1 = correct but not complete, 2 = correct). The interrater reliability of the mental state questions was good to very good, with *κ* values ranging from 0.57 to 1.00.

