### Procedure

Participants are recruited from the Bascule, an academic center for children and adolescent psychiatry in Amsterdam, the Netherlands. Approximately 270 children each year are referred to the center’s outpatient clinic for ASDs.

After obtaining informed consent from parents, children are randomized to an intervention or a waiting list control group. Importantly, children in both groups start their intervention 10 weeks after the moment of randomization. The children in the control group have their first assessment directly after the randomization, followed by a waiting period of 8 weeks. Their second assessment is one week prior to the start of the intervention. The children in the intervention group have their first assessment about 8 weeks after the moment of randomization, in the week directly prior to the start of their intervention. Their second assessment is immediately after the intervention. We collect follow-up data six months after ending the intervention.

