### Sample size

The sample size is based on the minimum effect size (Cohen’s *d* = 0.25) found in the intention-to-treat sample of the previous trial [12]. Based on an *α* of 0.05 and a power of 0.80, we need 40 subjects in each condition to demonstrate this effect size. The additional 20 participants allow for the analysis of the effects of the two moderator variables (social interactive style and disruptive behavior).

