#### Levels of Emotional Awareness Scale for Children (LEAS-C)

The LEAS-C [29] is a questionnaire to assess children’s emotional awareness. It contains 12 scenarios describing hypothetical social situations. Children are asked about how they would feel in the described situation. Children’s use of complex emotions (for example, guilt or embarrassment) and double perspective (highlighting both own and other person’s feelings) are coded. They can attribute these emotions to themselves (one point), the other person (two points) or to both (three points). Internal consistency has been shown to be moderate (α ranging from 0.64 to 0.71) and convergent validity acceptable [12,29].

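### Two of the three conceptual primary outcomes need a scorer's judgement, the assessment schedule gives away the arm at post-test, and no step is described that keeps this knowledge from the scorer

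*Protocol article*

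**What the plan says.** **Scoring.** The Protocol article lists three conceptual primary outcomes. The ToM test has 72 items marked right or wrong. The ToM advanced test grades each mental state answer on three levels ("0 = incorrect, 1 = correct but not complete, 2 = correct"), and its section reports agreement between raters: "The interrater reliability of the mental state questions was good to very good, with *κ* values ranging from 0.57 to 1.00". For the LEAS-C, "Children’s use of complex emotions (for example, guilt or embarrassment) and double perspective (highlighting both own and other person’s feelings) are coded", with one to three points according to whom the emotion is attributed.

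**Schedule (Procedure).** Both arms start the sessions 10 weeks after randomization. Control children are first assessed directly after randomization and again one week before their sessions begin. Intervention children are first assessed about 8 weeks after randomization. For them, "Their second assessment is immediately after the intervention".

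**Knowledge of allocation (Randomization).** The result goes to the primary investigator, who tells the parents.

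**Analysis and target.** The Statistical analysis section compares the arms on change. The Sample size section sets d = 0.25 as the effect to be detected.

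The article does not say who tests the children, who scores the answers, or whether scorers are masked.

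**The concern.** On two of the three conceptual measures a scorer has to decide whether an answer is complete, or whether it shows a complex emotion or a double perspective. A scorer who knows that a child has just finished the programme may, without intending to, give borderline answers the benefit of the doubt. The contrast is the between-arm difference in change, so leniency confined to intervention post-tests is added in full to the estimated effect. With a target of a quarter of a standard deviation, even a small directional shift matters.

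The schedule makes this more than a routine reminder about masking. Concealing the allocation list would not help, because the timing of the assessment relative to the sessions carries the same information. Only a deliberate separation of scoring from testing protects these two outcomes.

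**Working it through.** **1. Does the schedule reveal the arm?** Weeks are counted from randomization, using the Procedure and Intervention sections (sessions start at week 10; eight weekly sessions put the last one at 10 + 7 = week 17).

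| | First assessment | Second assessment | Sessions attended by then |
|---|---|---|---|
| Control | directly after randomization | one week before the start, about week 9 | 0 |
| Intervention | about week 8, in the week before the start | directly after the last session, week 17 or later | the full programme |

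At the second assessment the two arms share neither the calendar position nor the number of sessions behind them. Knowing that a child is being retested, and whether the sessions have taken place, is enough to identify the arm. A form that shows the date or time point passes this on to a later scorer.

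**2. Which outcomes are exposed?** The ToM advanced test and the LEAS-C, for the reasons under scoring. Right-or-wrong marking leaves less room on the ToM test, so it is not part of this point.

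**3. The yardstick.** The Sample size section states "of 0.05 and a power of 0.80, we need 40 subjects in each condition to demonstrate this effect size". For two means, n per arm = 2(1.960 + 0.842)² / 0.25², about 252 two-sided (198 one-sided). The stated 40 is not reproduced. With 40 per arm the two-sided power is about 20%, and roughly 40 per arm results only with an unstated pre-post correlation of about 0.92 on change scores. That is a separate matter. Here d = 0.25 serves only as the target against which a scoring shift is compared.

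**4. What would a scoring shift do? (illustration)** Inputs:
- 100 children, with 1:1 allocation assumed (50 per arm), and a two-sided 5% test.
- No true effect.
- An **assumed** shift b, in SD units of the score, at intervention post-tests only.

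The rejection probability comes from the noncentral t distribution with 98 degrees of freedom and noncentrality b·√(50/2) = 5b.
- b = 0.10: noncentrality 0.50, rejection 7.9%.
- b = 0.25: noncentrality 1.25, rejection 23.6%.

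On change scores the SD is √(2(1 − ρ)) times the score SD, where ρ is the pre-post correlation (not given, so assumed). The standardised shift is b/√(2(1 − ρ)).

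| ρ (assumed) | SD of change | b = 0.10 | b = 0.25 |
|---|---|---|---|
| 0.5 | 1.00 | 7.9% | 23.6% |
| 0.7 | 0.77 | 9.8% | 35.9% |
| 0.8 | 0.63 | 12.3% | 49.9% |

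The first row equals the simple calculation, because at ρ = 0.5 the change score has the same SD as the score itself. At higher correlations the same shift does more damage.

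**5. How much data is already collected?** The Trial status section reports 80% included and pretested, and 70% of those post-tested: 0.80 × 0.70 = 0.56, or about 56 of 100 children.

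**The case against.** The strongest reply is that this is a condensed article and that silence on masking is not a statement that scoring is open. That stands. A reader might infer that the scorers know the arm, but the documents do not say so. The point is limited to the absence of any described safeguard against a schedule that the article does describe.

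A second reply is that tester and scorer may be different people. The schedule identifies the arm to whoever sees the child in relation to the sessions, not to someone coding answers later from clean sheets. The reported agreement between raters fits scoring away from the session. This also stands, and it is why the remedy is feasible. It does not show that dates and time points were removed.

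Three stronger readings are not supported:
- **That the lower agreement values show bias.** Kappa measures how often raters agree, not in which direction they err. Non-directional disagreement adds noise and creates no group difference. The figure also covers the ToM advanced test only; none is given for the LEAS-C.
- **That the bias would be as large as the target effect.** The article gives no SD for either measure and no question count for the ToM advanced test. The upper end of the illustrated range is simply the target d, so it is an input and not a result.
- **That the training makes the answers themselves biased.** The fifth session covers emotions such as guilt and shame. The seventh covers first-order belief, with second-order questions only in its homework. Use of this vocabulary is partly what the LEAS-C is meant to measure. It may hint at treatment, which limits how complete any masking can be, but it is not bias in itself.

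**Conclusion.** The concern holds in a limited form. Two judgement-scored primary outcomes are combined with a schedule that discloses the arm at post-test, and the article describes nothing that keeps this from the scorer. Whether bias occurs, and how large it would be, cannot be determined from the document. The range of about 8% to 24% false positive results, rising to about 36% to 50% for a 0.25 SD shift on change scores at ρ = 0.7 to 0.8, rests wholly on the assumed shift, the assumed correlation, 1:1 allocation and no true effect. It shows how sensitive a target of d = 0.25 is to directional scoring and does not estimate what happened. The change is worth making because it is cheap and protects primary outcomes. It does not mean that the results on these measures are invalid.

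**What to change.** Record the ToM advanced test and LEAS-C answers verbatim at the session. Have the existing raters score them from sheets without identity, arm, date or time point, in random order, with both arms and both assessments mixed. If this is already the practice, a sentence saying so is enough.

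For children already assessed, rescore in the same way wherever the answers were recorded, and report how many could not be rescored, by arm and time point.

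The cost is the time to prepare and rescore the sheets, and later availability of the scores. No extra visits or raters are needed. Masking will remain imperfect, since trained vocabulary in an answer may still suggest treatment, and the report should say so.

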#### Levels of Emotional Awareness Scale for Children (LEAS-C)

The LEAS-C [29] is a questionnaire to assess children’s emotional awareness. It contains 12 scenarios describing hypothetical social situations. Children are asked about how they would feel in the described situation. Children’s use of complex emotions (for example, guilt or embarrassment) and double perspective (highlighting both own and other person’s feelings) are coded. They can attribute these emotions to themselves (one point), the other person (two points) or to both (three points). Internal consistency has been shown to be moderate (α ranging from 0.64 to 0.71) and convergent validity acceptable [12,29].

### Measures of primary outcomes: practical skills

#### Social Skills Questionnaire (SSQ)

Parent (SSQ-P) and teacher (SSQ-T) versions of the SSQ were used [30]. This is a widely used questionnaire designed to assess parents’ and teachers’ perceptions of the child’s social skills. The questionnaire contains 30 items, scored on a five-point Likert scale (0 = never true, 5 = always true). Internal consistency for the SSQ has been shown to be good, with a Guttman split-half reliability of 0.90.

#### Specific Social Behavior (SSB) questionnaire

The SSB questionnaire is a parent questionnaire designed specifically for this study to tap parents’ observations of specific theory of mind-related social behaviors displayed by their children. It contains eight items, scored on a five-point Likert scale (0 = never, 5 = always), that were based on information provided by parents during meetings set up to evaluate the intervention. Parents are asked to rate the frequency of specific theory of mind-related social behaviors.

### Measures of moderating variables

#### Wing Subgroups Questionnaire (WSQ)

The WSQ [31] is a parent questionnaire to determine the Wing social subtype of a child with ASD (aloof, passive, or active-but-odd). The WSQ contains 13 groups of four different descriptions of social behavior; each of these four descriptions characterizes one of the three Wing subtypes or a normal response. Parents evaluate how well each description fits their child on a seven-point Likert scale ranging from 0 (never) to 6 (always). Parents also choose one of each four descriptions that fit their child best. The internal consistency of the WSQ is moderate to good [17,31,32].

#### Disruptive Behavior Disorders rating scale (DBD)

The DBD rating scale [33] is a parent questionnaire to assess the symptoms of a disruptive behavior disorder in children between 6 and 16 years old. The DBD rating scale contains 42 descriptions of behavior, distinguishing between four subscales: attention deficits (9 items), hyperactivity or impulsivity (9 items), oppositional-defiant disorder (8 items), and conduct disorder (16 items). Parents evaluate how well each description fits their child on a four-point Likert scale from 1 (not at all) to 4 (a lot). Adequate psychometric properties of the DBD have been reported [33].

### Measures of control variables

#### Peabody Picture Vocabulary Test – III-NL (PPVT)

The PPVT [34] is a receptive language and screening test for verbal comprehension. It is highly correlated with a more general measure of verbal IQ, the WISC-III verbal IQ [35]. The test contains 17 sets with 12 items each, the child’s age determines the set at which the child starts. With nine or more incorrect items in one set, the test ends. The children are shown four pictures and read one word describing one of the pictures. Children need to identify the corresponding picture. A verbal IQ standardized score for age is then obtained. The PPVT has been found reliable and valid [36].

#### Social Responsiveness Scale (SRS)

The SRS [22] is a parent questionnaire designed to assess autistic traits. The SRS contains 65 descriptions of a child’s behavior, which are arranged in five subscales: social awareness, social cognition, social communication, social motivation, and autistic manners. Parents evaluate how well each description fits their child on a four-point Likert scale ranging from 0 (never true) to 3 (almost always true), and item scores are added to subscale scores. Good reliability and validity have been reported [22].

### Statistical analysis

Baseline differences in demographic and clinical characteristics will be investigated using chi-square tests and analyses of variance. To test intervention efficacy analyses of variance will be performed to compare differences between intervention group and waiting list control group in change in conceptual and practical skills. Between-group effect sizes will be calculated according to Cohen’s *d*. To test moderating effects of social interaction style (SIS) and disruptive behavior (DB) Group × SIS and Group × DB effects on change in conceptual and practical skills will be tested using multiple regression analyses, controlling for the severity of the autistic disorder and intellectual ability.

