**Methods:**

This study is a randomized controlled trial. One hundred children with ASD, aged 7 to 12 years will be randomly assigned to an intervention or a waiting list control group. Outcome measures include the completion of theory of mind and emotion understanding tasks, and parent and teacher questionnaires on children’s social skills. Follow-up data for the intervention group will be collected 6 months after the interventions.

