### Randomization

Randomization takes place 9 to 10 weeks before the start of the intervention. An independent research colleague randomizes the children using a digital random number generator. The randomization outcome is shared with the primary investigator, who informs parents about the condition.

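### Treatment is given in groups of five or six, but the named child-level ANOVA and regressions assume independent children; any positive treatment-induced within-group correlation pushes type I error above 5%

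*Protocol article*

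**What the plan says.** All references are to the protocol article.

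- **Randomization:** allocation is by child. "An independent research colleague randomizes the children using a digital random number generator".
- **Intervention:** eight weekly sessions of about an hour, "provided to five or six children simultaneously, with a mutual age difference that does not exceed 3 years". On staffing: "Each session will be supervised by one or two certified therapists". The session descriptions include games, role-plays, discussion and joint plays, so interaction among group members is part of the treatment.
- **Procedure:** for control children, "Their second assessment is one week prior to the start of the intervention". They have had no group treatment when the arms are compared.
- **Statistical analysis:** "To test intervention efficacy analyses of variance will be performed to compare differences between intervention group and waiting list control group", on change in conceptual and practical skills. The Group × social interaction style and Group × disruptive behavior effects "will be tested using multiple regression analyses, controlling for the severity of the autistic disorder and intellectual ability".

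Neither analysis has a term for training group or therapist. The Sample size section applies no design effect, and the article does not mention clustering anywhere.

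**The concern.** At the comparison this is a partially nested design. Children in the intervention arm have shared a training group and its therapists for eight weeks; control children have shared nothing through treatment. If some groups go better than others because of the therapist or the mix of peers, changes within a group are positively correlated. The mean of the intervention arm is then less precise than its number of children suggests.

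A standard ANOVA or ordinary regression does not see this. Its standard error is too small, its confidence interval too narrow, and a true null hypothesis is rejected more often than the stated 0.05. The error favours declaring the treatment effective. It can affect any of the primary outcomes, to a degree that may differ between child-tested tasks, parent reports and teacher reports. It also reaches the moderator models, which serve the trial's second objective.

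**Working it through.** The article gives no figure for clustering, so there is none to reproduce. The intraclass correlations of 0.80 to 0.99 quoted for the ToM test are test-retest reliabilities and do not bear on this.

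**Inputs**

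- Total sample 100, from the abstract: "One hundred children with ASD, aged 7 to 12 years will be randomly assigned to an intervention or a waiting list control group". No allocation ratio is given; 50 per arm is assumed.
- Significance level and power, from Sample size: "Based on an *α* of 0.05 and a power of 0.80". Two-sided testing is assumed.
- Group size five or six, from Intervention. If training groups contain one arm only, 50 children fit nine groups (five of six and four of five: 30 + 20 = 50), with mean size m = 50/9 = 5.56. That groups contain one arm only is an assumption.
- ICC of change scores within training groups: not given. Range shown: 0 to 0.30.

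**Formulas**, with equal total variance in the two arms

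- Design effect in the intervention arm: DE = 1 + (m − 1) × ICC.
- True over naive variance of the difference in means: R = (DE + 1)/2, because only one arm is clustered.
- Share by which the naive variance is too small: 1 − 1/R.
- Approximate type I error: 2 × [1 − Φ(1.96/√R)].

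**Worked case, ICC 0.10.** DE = 1 + 4.56 × 0.10 = 1.456. R = 2.456/2 = 1.228. True variance exceeds naive variance by 23%; equivalently, naive variance is too small by 1 − 1/1.228 = 19%. Type I error is 2 × [1 − Φ(1.96/1.108)] = 7.7%. The 50 treated children carry the information of 50/1.456, or about 34.

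**Nine intervention-only groups**

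| ICC | DE | R | True variance above naive | Naive variance too small by | Type I error, formula | Type I error, simulated |
|---|---|---|---|---|---|---|
| 0 | 1.00 | 1.00 | 0% | 0% | 5.0% | about 5% |
| 0.01 | 1.05 | 1.02 | 2% | 2% | 5.3% | about 5% |
| 0.05 | 1.23 | 1.11 | 11% | 10% | 6.3% | 6.3% |
| 0.10 | 1.46 | 1.23 | 23% | 19% | 7.7% | 7.8% |
| 0.20 | 1.91 | 1.46 | 46% | 31% | 10.4% | 10.5% |
| 0.30 | 2.37 | 1.68 | 68% | 41% | 13.1% | 12.9% |

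**Training groups that mix the arms.** The Procedure section has children of both arms start treatment 10 weeks after randomization, and nothing says that groups are kept to one arm. If they are mixed, 100 children form about 18 groups, with 50/18 = 2.78 intervention-arm children in each. Then DE = 1 + 1.78 × ICC, and the formula gives 5.5%, 6.0%, 7.1% and 8.2% at ICC 0.05, 0.10, 0.20 and 0.30. Simulation gives 5.8% to 8.3% over the same range.

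**Age banding.** Change scores related to age were simulated with age-sorted training groups and no group effect. The apparent ICC reached 0.30, yet the child-level test rejected in 4.9% to 5.3% of trials, which is nominal. A test on training-group means without age adjustment rejected in only 1.1%, which is overcorrection.

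**The case against.** **Inflation is conditional.** A reader might infer that the planned test necessarily exceeds 5% for every primary outcome. The article does not support that: it gives no clustering ICC for any outcome, and at ICC 0 to 0.01 the test is close to nominal. If treatment changes no child at all, there is no treatment-induced clustering and individual randomization protects the test. Inflation requires groups or therapists that shift outcomes differently while the average effect is zero. This objection stands and limits the claim.

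**Age bands.** It is tempting to count the three-year age limit as a further source of inflation. It is not one. Sorting an arm by age after individual randomization leaves the variance of the arm mean unchanged, as the simulation shows. It does matter for the remedy, because a training-group correction without age can be too conservative.

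**Nine clusters.** The article does not say that training groups contain one arm only. With mixed groups the excess over 5% is roughly 40% to 60% of that shown in the table. The larger figures must therefore carry their assumption.

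**A condensed article.** A random effect and a method for degrees of freedom may be set out in a full plan that is not shown. That is fair as to detail, and silence does not prove that clustering will be ignored. But the article does not leave the method open. It names ANOVA as the efficacy test and lists the covariates of the moderator regressions. As stated, these methods do not match the way treatment is delivered.

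**Conclusion.** The point holds in conditional form. The named ANOVA and regressions are anti-conservative for any positive within-group correlation in change that is induced by shared sessions and therapists. Interactive sessions with common therapists make such a correlation plausible, but the article does not establish it.

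Assuming 50 per arm, two-sided testing and nine intervention-only groups, type I error runs from about 5% at ICC 0 to 0.01, through 6.3% at 0.05 and 8% at 0.10, to 10.5% at 0.20 and 13% at 0.30. With mixed training groups it is about 6% to 8% over ICC 0.05 to 0.30. The distortion is modest at small ICCs and serious at large ones. Because the plan cannot know in advance which applies, the analysis should allow for it.

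**What to change.** Replace the ANOVA on change with a partially nested linear mixed model:

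- outcome at the second assessment, adjusted for the baseline score and for age, the latter so that age-banded groups do not cause overcorrection;
- a random training-group effect for intervention-arm children only, with control children treated as independent at this comparison, whether or not they later join mixed groups;
- Satterthwaite or Kenward-Roger degrees of freedom, because there are few groups.

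Use the same structure for the Group × social interaction style and Group × disruptive behavior models, keeping the covariates already named. Record each child's training-group identifier, state whether groups contain one arm or both, and report the estimated ICC for each outcome.

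The cost is analysis wording and one variable; valid inference needs no change of design and no extra children. The Trial status section reports 80% of participants included and 70% of those post-tested (0.80 × 0.70 = 56% of the planned sample), so group membership should still be recoverable. The downside is wider confidence intervals, noticeably so if the ICC is large: on the nine-group assumption the true standard error exceeds the naive one by about 5% at ICC 0.05 (√1.11) and 30% at ICC 0.30 (√1.68).

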## Trial status

At the time of submission, 80% of the participants have been included in the treatment study, and pretested. Of these participants, 70% were also post tested.

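### Efficacy rests on change scores that need about 9 weeks' retention from randomisation in control but about 18 in intervention, so the arms are exposed to unequal attrition

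*Protocol article*

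**What the plan says.** The Statistical analysis section of the protocol article states that "analyses of variance will be performed to compare differences between intervention group and waiting list control group in change in conceptual and practical skills". The moderator regressions in the same section also take change as the outcome.

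The Procedure section fixes when the two assessments occur:

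- Both arms: "children in both groups start their intervention 10 weeks after the moment of randomization".
- Control: "The children in the control group have their first assessment directly after the randomization, followed by a waiting period of 8 weeks". Then: "Their second assessment is one week prior to the start of the intervention".
- Intervention: "The children in the intervention group have their first assessment about 8 weeks after the moment of randomization". Then: "Their second assessment is immediately after the intervention".

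The Intervention section describes eight weekly sessions. The Randomization section says that parents are told the condition once the allocation is known.

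**The concern.** Having both assessments means something different in each arm. A control child qualifies by staying through one waiting period. An intervention child must stay through a similar wait and then remain available until the programme has ended.

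The wait also leaves a different record in each arm. The control arm is measured at its start, the intervention arm only near its end. A family that leaves the intervention arm in the first 8 weeks, after learning its allocation, leaves no outcome data.

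What is at stake is the randomised comparison. If children who leave would have changed differently from those who stay, the arm that loses more children is shifted more, and the difference in mean change no longer estimates the effect among all children randomised. The moderator regressions use the same children and inherit the problem.

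**Working it through.** The article gives no attrition or retention figure, so there is none to reproduce. The check is a timeline from the article, followed by an illustration on assumed inputs.

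**Timeline from randomisation (Procedure and Intervention sections)**

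- Control, first assessment: about week 0.
- Control, second assessment: 10 − 1 = about week 9.
- Intervention, first assessment: about week 8 to 9.
- Intervention, second assessment: 10 + 8 = about week 18.

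First to second assessment takes about 9 weeks in both arms. The asymmetry appears only when retention is counted from randomisation: about 9 weeks against about 18.

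**Assumptions (not in the article)**

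- 50 children randomised per arm, that is, 100 split equally.
- The same withdrawal fraction x per 9 weeks in both arms, with withdrawn children not assessed afterwards.
- In each arm, withdrawers would have changed g SD less than those who stay.

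**Formulas**

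- Share with a change score: (1 − x) in control and (1 − x)² in intervention.
- In an arm that loses a fraction L, the mean of those remaining exceeds the mean of all randomised by g × L.
- Bias in the group difference: g × [1 − (1 − x)²] − g × x = g × x × (1 − x).
- Ratio of losses, intervention to control: [1 − (1 − x)²] / x = 2 − x.

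| x per 9 weeks | Control with change score | Intervention with change score | Bias, g = 0.5 | Bias, g = 1.0 |
|---|---|---|---|---|
| 0% | 50 | 50 | 0 | 0 |
| 5% | 47.5 | 45.1 | 0.024 | 0.048 |
| 10% | 45 | 40.5 | 0.045 | 0.090 |
| 15% | 42.5 | 36.1 | 0.064 | 0.128 |
| 20% | 40 | 32 | 0.080 | 0.160 |

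The ratio of losses is 2 − 0.05 = 1.95 at x = 5% and 2 − 0.20 = 1.8 at x = 20%. The intervention arm therefore loses nearly twice as many children even if nobody leaves because of the programme.

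Against the planning effect of 0.25 in the Sample size section, the g = 0.5 biases run from 0.024 / 0.25 = about 10% to 0.080 / 0.25 = 32%. This comparison takes d and the bias to be on the same SD scale; the article does not say which SD its d uses.

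**Sign.** With g positive, the bias favours the intervention. If withdrawers would have changed more than those who stay, the sign reverses.

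**The case against.** The strongest reply is that the article names a test and no analysis set. It does not say that withdrawn children are excluded, and it does not rule out imputation. A child who stops attending sessions could still be assessed at the scheduled time. Missing-data handling is commonly left to a full protocol or analysis plan, and none is shown here. All of this stands. A reader might infer that the trial will report a completers-only comparison; the article does not say so.

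Two further inferences are tempting and also fail.

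- The planning effect was "found in the intention-to-treat sample of the previous trial". This might be read as contradicting a change-score analysis. It is only a planning input and does not fix the analysis set of the present trial.
- The Trial status section reports that "80% of the participants have been included in the treatment study, and pretested". This might suggest that early withdrawals are left out of the count. It is an accrual statement at submission and says nothing about dropout.

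The size and direction of any bias are also assumed. The Discussion section expects disruptive behaviour to limit benefit; it does not say that such children leave more often. Children who leave during the wait have attended no session, so poor response to the programme cannot explain their leaving.

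The objection does not remove the asymmetry. That follows from the stated schedule together with the stated outcome, not from silence. A later missing-data rule would also have no outcome baseline to work from for an intervention child lost before about week 8.

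**Conclusion.** The point holds as a conditional one. The staggered schedule requires about twice the retention from randomisation in the intervention arm, and an analysis of variance on change does not by itself protect the randomised comparison against the result.

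Under equal withdrawal of 5% to 20% per 9 weeks, and a 0.5 SD shortfall in change among withdrawers, the bias is about 0.02 to 0.08 SD against a planning effect of 0.25. With no withdrawal, or withdrawal unrelated to change, it is zero. The direction is uncertain for losses during the wait. The article does not establish that biased loss has occurred or that withdrawn children will be left out. The change is worth making because it costs little.

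**What to change.** 1. State that both assessments are sought at their scheduled times for every randomised child, whether or not sessions were missed or stopped.
2. Analyse children in their assigned arm with a likelihood-based repeated-measures model. Take both assessments as outcomes and the group-by-time contrast as the effect, so that children with only one assessment stay in.
3. Report losses by arm, counted from randomisation: before the first assessment, and between the first and the second.
4. Keep the change-score analysis of variance as a sensitivity analysis.

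**Cost.** A change to the analysis text, and a few extra post-tests with instruments already in use. By the Trial status section, 0.80 × 0.70 = 56% of participants had been post-tested at submission. Step 1 can therefore help mainly the remaining 44%, and assessments missed earlier may not be recoverable on schedule.

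**Limits.** The model assumes that data are missing at random. It recovers nothing for a child with no assessment, and it does not correct loss that depends on unobserved change. For those children only obtaining the assessment helps, so step 1 matters most.
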